### Sample Size and Statistical Power

We reviewed stroke and cardiovascular intervention programs to estimate the sample size required for this study [21,46]. Sample size consideration and power analyses were performed based on the primary outcome variable of systolic blood pressure. Using an SD of 21 mm HG with an alpha significance level of.05 and two-sided *t* test analyses, we estimated that 150 participants per study arm (300 participants total) could detect a minimum difference of 8 mm HG between groups with 91% power. This is smaller than the 10 mm Hg threshold in secondary stroke prevention guidelines [47]. For our secondary outcome of low-density lipoprotein), we will have 80% power to detect a minimum low-density lipoprotein difference of 13 mg/dL given SD of 39 mg/dL. For adherence to antiplatelet or antithrombotic therapy, we will have 83% power to detect a 15% difference in adherence among the intervention versus control group. All data will be analyzed using the latest SAS software (Cary, NC).

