### Primary Outcome

The primary outcome is a change in systolic blood pressure from baseline to the 12-month evaluation as measured using the Omron HEM-705CP automated oscillometric device (Lake Forest, IL, USA). Following the American Heart Association guidelines, 3 readings are taken, and the average of the last 2 readings is used as the blood pressure measurement [48]. The study is powered to test the hypothesis that at 1 year, systolic blood pressure of participants enrolled in the intervention will be 8 mm HG lower than those in the control (see below).

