### Confounding Variables

Potential confounders of our primary and secondary outcomes include sociodemographics (age, sex, income, and educational attainment); health insurance status; depression (Center for Epidemiological Studies Depression Scale) [51]; acculturation (modified Marin-Marin scale) [52,53]; health literacy (Short Assessment of Health Literacy-Spanish and English) validated in both English and Spanish) [54]; body mass index; and functional status (modified Rankin score) [32].

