### Statistical Analysis

The distribution of baseline values and outcomes will be examined for each arm. The intervention effects on outcomes (systolic blood pressure, low-density lipoprotein, and glycated hemaglobin) will be evaluated using linear regression models for continuous variables as a function of intervention status as well as with categorical classification variables to index time intervals pre- and postintervention. We will use statistical tests of the estimates of the regression parameters from this model to compare the major outcomes before and after the intervention groups in the full sample as well as between intervention groups. Adherence to antiplatelet or antithrombotic therapy will also be evaluated using logistic regression models as a function of intervention status. Covariates that will be included in the models will include age, sex, body mass index, and educational attainment. Relationships between the outcome variables and other potential covariates such as income, health insurance status, health literacy, and functional status will be explored to determine their potential inclusion in final models.

**Table 1 table1:** List of variables and measures included in Hispanic Secondary Stroke Prevention Initiative baseline survey.

Variables		Measures or methods

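### Covariates for the final models, including the primary blood pressure model, are to be settled after exploring their relation to the outcomes, so no single primary model is fixed in advance

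*Protocol article*

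**What the plan says.** The Primary Outcome section defines the endpoint: "The primary outcome is a change in systolic blood pressure from baseline to the 12-month evaluation". The Statistical Analysis section gives the modelling approach: "The intervention effects on outcomes (systolic blood pressure, low-density lipoprotein, and glycated hemaglobin) will be evaluated using linear regression models". The model contains intervention status and a classification for the periods before and after the intervention. Adherence to antiplatelet or antithrombotic therapy gets a logistic model.

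The same section fixes part of the covariate set: "Covariates that will be included in the models will include age, sex, body mass index, and educational attainment". The next sentence leaves the rest open: "Relationships between the outcome variables and other potential covariates such as income, health insurance status, health literacy, and functional status will be explored". Four further variables are given as examples, and their relationships with the outcomes "will be explored to determine their potential inclusion in final models". The outcomes are not restricted to the secondary ones, so the sentence reaches the blood pressure model.

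The Confounding Variables section has a longer list, which begins "Potential confounders of our primary and secondary outcomes include sociodemographics (age, sex, income, and educational attainment); health insurance status; depression" and goes on to acculturation, health literacy, body mass index and functional status. The Randomization and Blinding section states 1:1 allocation within each hospital. Hospital is not among the fixed covariates.

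**The concern.** The sentence makes the final primary model depend on outcome data. Four optional covariates allow 2^4 = 16 final models, and the four are only examples. Several models could then each be called the planned analysis. A reader of a borderline result could not tell whether the reported one was chosen for its prognostic content or for its treatment estimate.

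The usual reason for such a step, control of confounding, has little force here. Under 1:1 randomisation, baseline covariates serve mainly to gain precision, and prespecification secures that gain without the ambiguity. For adherence there is a further cost. A conditional odds ratio changes with the covariates conditioned on, so an open set leaves the quantity being estimated undefined.

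At stake are the credibility of the primary result and, in the worst case, its 5% significance level.

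**Working it through.** **Inputs from the article.** 150 per arm, difference 8 mm Hg, SD 21 mm Hg, two-sided alpha 0.05, stated power 91% (Sample Size and Statistical Power); expected attrition about 10%, and 21% in a prior study (Limitations); four fixed and four named optional covariates (Statistical Analysis).

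**The plan's own figure.** The standard error of the difference is 21 × √(2/150) = 2.425 mm Hg. Then 8/2.425 = 3.299, 3.299 − 1.960 = 1.339, and Φ(1.339) = 0.910. The noncentral t gives 0.908. The stated 91% reproduces. It comes from an unadjusted two-sample comparison, so it does not rely on the optional covariates.

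**Type I error by selection rule.** Data were simulated with no treatment effect, 1:1 allocation and linear regression, 4,000 runs per setting. The Monte Carlo standard error at 5% is √(0.05 × 0.95/4000) = 0.34 percentage points. Three things are assumed because the article gives no values: the fixed covariates explain 10% of outcome variance, the optional ones jointly explain the R² shown, and all covariates are independent. N = 236 corresponds to 21% attrition. Six optional covariates illustrate the open pool.

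| N, optional covariates, joint R² | Fixed set only | Add if outcome association p < 0.10, ignoring treatment | Keep if p < 0.05 in full model | Subset most favourable to treatment |
|---|---|---|---|---|
| 300, 4, 0 | 5.53% | 5.38% | 5.55% | 6.48% |
| 300, 4, 0.10 | 4.85% | 4.70% | 4.98% | 8.35% |
| 300, 4, 0.20 | 4.83% | 4.48% | 4.50% | 9.93% |
| 236, 4, 0.10 | 5.60% | 5.95% | 6.00% | 9.83% |
| 300, 6, 0.10 | 5.23% | 5.45% | 5.75% | 10.65% |
| 300, 6, 0.20 | 5.08% | 5.13% | 5.28% | 13.50% |

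The two rules based on outcome association stay within about 0.5 points of the fixed set. That is expected: with no treatment effect, a choice made from outcomes and baseline covariates alone carries no information about allocation.

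**Second setting.** N = 300 × 0.90 = 270, four optional covariates with standardised coefficients 0.1, 0.2 or 0.3, 6,000 replicates:

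- Fixed model: 5.0%, 5.0%, 5.7%.
- Add if outcome association p < 0.10: 4.8%, 5.1%, 5.7%.
- Keep if p < 0.05: 5.0%, 5.2%, 5.7%.
- Most favourable of 16 models, two separate runs: 7.8%, 9.1%, 13.5% and 7.1%, 9.2%, 12.6%.

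The 0.3 case is generous. With unit residual variance it implies 4 × 0.3² / (1 + 4 × 0.3²) = 0.36/1.36, or about 26% of variance explained by the optional covariates.

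**The case against.** The strongest reply is that the article describes looking at outcome–covariate relationships, not comparing treatment p-values across models. A reader might infer that the plan as written inflates type I error and that its 5% level no longer holds. The documents do not support this. Under the procedure described, the simulated error stays near 5%. The 7% to 14% figures belong to a different procedure, picking the model by its treatment result, which the article nowhere proposes. This part of the objection stands.

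A second reply is that a selection criterion and its timing belong in a statistical analysis plan, which is not shown. As far as it goes, that is right, and their absence is not the point made here. The exploratory step itself is stated in the article, however, and a plan that fixed the covariates would depart from the published sentence.

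Third, a reader might infer from the Confounding Variables section that depression and acculturation are candidates for the final model. That section only lists potential confounders and does not say so. The pool is open because the Statistical Analysis section names its four variables as examples.

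What remains is that the article does not show the harmless form of selection to be the only one available. It has the distribution of outcomes examined for each arm. It names the principal investigator and the clinical coordinator as blinded, but not the biostatistician, who performs the randomisation. None of this shows that models will be chosen on the treatment estimate. It only means that the article does not exclude it.

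**Conclusion.** The point holds in limited form. The article states an outcome-informed, open-ended route into the final models and so leaves the primary estimate to analyst choice. Inflated type I error is a possibility, not a certainty: about 4.5% to 6.0% if selection ignores treatment, and roughly 7% to 14% in the worst case where the treatment estimate guides the choice. The worst-case range rests on assumed covariate strengths (joint R² of 0 to 0.20, or standardised coefficients of 0.1 to 0.3), on four or six independent optional covariates, and on an exhaustive search for the most favourable model. The defect should be corrected because it exposes a borderline result to challenge and costs almost nothing to remove. It does not invalidate the design.

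**What to change.** - Prespecify the covariates of the primary model as age, sex, body mass index and education, plus hospital, because randomisation is within hospital.
- State one treatment of baseline blood pressure: either a covariate in a model for 12-month systolic blood pressure, or a response in the pre/post model the article describes. It should not be both.
- Delete the exploratory inclusion step for the primary and secondary tests, or replace it with an explicit rule applied blind to allocation.
- Report income, health insurance, health literacy and functional status together in one named sensitivity model, whatever it shows.

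The cost is analysis wording. Sample size and the stated 91% power are unchanged. The downside is some lost precision if an omitted covariate proves strongly prognostic. Under the simulation's assumptions, omitting covariates that explain a further 10% of variance widens the confidence interval by a factor of √(0.90/0.80) = 1.06, and at 20% by √(0.90/0.70) = 1.13. A variable already believed to be that strong can be added to the fixed set now.

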**Primary outcomes**		
	Blood pressure [48]	OMRON HEM-705CP, validated oscillometric device
**Secondary outcomes**		
	Low-density lipoprotein [49]	Roche Cobas c501 (Friedewald equation), also registry
	Glycated hemaglobin	Bio-Rad D-10 Latex agglutination, also from registry
	Adherence to antiplatelet or antithrombotic medication [50]	Medication Adherence Scale
**Exploratory outcomes**		
	Quality of life [55,56]	EuroQual (NINDS CDE^a^ core)
	Visits to providers	Agency for Healthcare Research and Quality Medical Expenditure Panel Survey
	Hospitalization or stroke admissions [57]	Medical Expedinture Panel Survey and Northern Manhattan Study Questions
**Mechanistic variables (mediators)**		
	Blood Pressure Behaviors Compliance [58]	Hill Bone Scale (salt intake & blood pressure medication adherence)
	Fruit and Vegetable Intake [59]	Behavioral Risk Factor Surveillance System (as a very rough marker of any diet change)
	Medication Intensification [20]	Miami Healthy Heart Initiative Medication Intensification Criteria
	Physical Activity [60]	International Physical Activity Questionnaire, Common Data Elements
**Covariates (moderators)**		
	Sociodemographics	NINDS CDE (core)
	Acculturation [53]	Marin-Marin (5 items)
	Health Literacy [54]	Short Assessment of Health Literacy-Spanish and English
	Depression [51]	Center for Epidemiologic Studies Depression (NINDS CDE core)
	Body mass index	Genentech Stadiometer, Platform Scale
	Functional status [32,33]	Modified Rankin Scale (NINDS CDE core)

^a^NINDS CDE: National Institute of Neurological Disorders and Stroke Common Data Elements.

## Results

Funding for the study began on 2014 and the first participant was enrolled on February 26, 2015. Enrollment is planned to be completed by 2018, and a manuscript describing the baseline characteristics of the population is expected to be completed by 2019 and submitted for publication in 2020.

## Discussion

### Limitations

Study attrition is a concern. In a prior diabetes study, we experienced 21% attrition [21]. As Figure 1 shows, even with such attrition, we would have >80% power to detect an systolic blood pressure difference of 8 mm HG. However, in that study, patients were younger and a much more geographically mobile group than stroke survivors. Thus, for HiSSPI, we expect an attrition rate of about 10%. Analytically, attrition will be handled by examining baseline characteristics of completers and noncompleters and testing patterns of attrition for randomness or ignorability. If the pattern of missing data is nonignorable, 1 approach is using baseline values carried forward. However, baseline values carried forward may not be the best method, and sensitivity analyses will be considered using different approaches such as weighted generalized estimating equations (using the inverse probability of dropout), multiple imputation, and propensity scores [61,62].

As noted above, Miami has a diverse Latino population of Caribbean, Central, and South Americans facing numerous distinct barriers to quality stroke care. Thus, it is an ideal location to generate findings that generalize to the US Latino population. In addition, initially, we also considered having Puerto Rico as another recruitment site. This site would allow us to test the intervention in a more homogenous Latino population where barriers such as immigration status and language are mitigated. Unfortunately, budgetary constraints did not allow us to include this site.

Lastly, a gap in the CHW literature is that few studies model the costs and benefits of CHW programs. Our proposed intervention of having one CHW assigned to a panel of 25-30 patients is costs approximately US $2000 per patient. Even though this figure pales in comparison with the cost of a subsequent stroke, of key importance to policy makers would be a formal cost-effective analysis. Although a formal cost-effective analysis is not part of the protocol, as part of the survey instrument, we will be collecting quality of life data using a standardized health state instrument (EQ5) and collecting data on health care utilization and hospitalizations. If linked to expenditure data, such data would allow for a future cost-effective evaluation.

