### Randomization and Blinding

Patients are randomized at a 1:1 ratio to the enhanced care group or the CHW intervention group within each hospital. Within each site, every eligible patient receives a unique study subject identification number and the prespecified assignment that corresponds to the identification number through randomization. The principal investigator and the program clinical coordinator are blinded to study allocation. However, both participants and CHWs are aware of the group to which each participant was randomized.

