### Control Arm: Enhanced Usual Care

Patients randomized into this group receive enhanced usual care. Depending on the stroke severity, patients at both facilities are either discharged home or to a short-term rehabilitation facility. Prior to release, the patient’s nurse or case manager ensures the patient is scheduled for a follow-up with their primary care provider and a neurologist. Patients lacking a primary care provider are provided with a list of potential follow-up care facilities and information on how to schedule an appointment.

For this project, participants in the control group also receive health education materials every 4 months including the following: “Lo que necesita saber sobre los ataques cerebrales,” a National Institute of Neurological Disorders and Stroke brochure that explains the causes of stroke, the associated risk factors, and strategies for prevention [35]; “Cómo prepararse para una cita con el medico,” a booklet that provides guidance, strategies, and tips to Latino patients on ways to better communicate with their physician [36]; and a National Heart, Lung, and Blood Institute bilingual Latino recipe cookbook [37].

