### Maintenance Phase (Months 4-12)

During the maintenance phase, participants are expected to independently maintain progress on their patient navigation activities and individual lifestyle intervention goals. CHWs contact participants weekly by phone to check on their progress including the status of participant action plans, updates on lifestyle modifications, and addressing new problems that may have developed. Participants also initiate contact with CHWs when in need of additional support. Phone calls are also used for patient navigation purposes including reminding participants of their next doctor’s appointment and facilitating patient contact with their provider offices when needed. Home visits can also occur during this period to ensure participants are meeting their outlined goals. During the final contact, participants are notified that the intervention is concluding and that they will be contacted in the coming weeks to complete their follow-up visit at the University of Miami Clinical Research Center.

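### The choice of missing-data method depends on an ignorability test that observed data cannot supply, and the one method tied to nonignorable dropout, baseline carried forward, does not model it

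*Protocol article*

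**What the plan says.** The handling of attrition is set out in the Limitations part of the Discussion; the Statistical Analysis section has no missing-data rule. The Limitations text has three steps.

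1. Completers and noncompleters are compared on baseline characteristics, together with "testing patterns of attrition for randomness or ignorability".
2. A conditional follows: "If the pattern of missing data is nonignorable, 1 approach is using baseline values carried forward". The next sentence concedes that this may not be the best choice.
3. Sensitivity analyses are to be considered, with "weighted generalized estimating equations (using the inverse probability of dropout), multiple imputation, and propensity scores" given as examples.

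The same section expects attrition of about 10% and reports 21% in a prior diabetes study. Contact differs by arm. In the intervention arm's maintenance phase, "CHWs contact participants weekly by phone to check on their progress", whereas "participants in the control group also receive health education materials every 4 months".

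**The concern.** Dropout is ignorable or not according to whether, given what was observed, it still depends on the 12-month systolic pressure that is missing. A comparison at baseline says nothing about that. The conditional in step 2 therefore has no valid trigger. In practice a baseline difference between completers and noncompleters, which is fully compatible with missing at random, could be read as nonignorable and lead to the weaker method.

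That method does not represent nonignorable dropout. It is one fixed assumption: no dropout's pressure changed at all. If that is wrong, the treatment difference is diluted or shifted. The alternatives in step 3 are sounder, but none is stated in a form that lets dropouts differ systematically from comparable completers. The nonignorable case that the paragraph raises would then go unexamined. Because contact is so unequal, attrition that differs by arm is plausible.

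**Working it through.** **Inputs from the article.** SD 21 mm Hg, two-sided alpha 0.05, 150 per arm, difference 8 mm Hg, stated power 91% (Sample Size and Statistical Power); 1:1 allocation (Randomization and Blinding); attrition about 10% expected and 21% in the prior study, with power above 80% claimed at 21% (Limitations).

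**Assumptions not in the article.** A fall of 5 to 10 mm Hg shared by both arms; the splits of attrition between arms; and how far dropouts depart from their missing-at-random prediction.

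**The plan's own figures.** Power = Φ(8 / [21·√(2/n)] − 1.96).
- n = 150: standard error 2.42; 8/2.42 = 3.30; power 91.0%. This agrees with the stated 91%.
- n = 118 (21% lost): standard error 2.73; power 83.3%. This agrees with the claim of more than 80%.
- n = 135 (10% lost): power 87.9%.

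These figures are not in dispute. They treat attrition only as lost sample size.

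**Baseline carried forward, equal attrition d.** Each dropout contributes a change of 0, so an arm's expected mean change is (1 − d) × the completer mean. If dropouts would have had the same effect as completers:
- d = 0.10: 8 × 0.90 = 7.2 mm Hg.
- d = 0.21: 8 × 0.79 = 6.32 mm Hg.

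**Baseline carried forward, unequal attrition, no true effect.** With a shared fall F, the spurious difference is F × (difference in attrition).

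| Attrition in the two arms | F = 5 | F = 10 |
|---|---|---|
| 6.7% and 13.3% (average 10%) | 0.33 | 0.67 |
| 10% and 21% | 0.55 | 1.10 |
| 14% and 28% (average 21%) | 0.70 | 1.40 |

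The arm that loses more looks worse, so the sign depends on which arm that is. For 10% and 21%, with SD 21 taken for completers' change, type I error is about 0.057 (F = 5) to 0.077 (F = 10) in place of 0.05. The biases compare with a standard error of about 2.4 mm Hg at full enrolment.

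**What the missing-at-random methods leave open.** If intervention dropouts are s mm Hg worse than their missing-at-random prediction, the true effect behind an estimate of 8 is 8 − d·s.
- d = 0.10, s = 5 to 20: 7.5 to 6.0 mm Hg.
- d = 0.21, s = 5 to 20: 6.95 to 3.8 mm Hg.

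Every value of s fits the observed data equally well. No test on those data can choose among them, so the size of the departure has to be varied by assumption.

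**The case against.** The strongest reply is that the article commits to very little. It offers baseline carried forward as one option and doubts it at once. Its list of alternatives is illustrative, and multiple imputation can be run under missing not at random. The randomness half of the planned test is partly checkable, and comparing completers with noncompleters is good practice. All of this stands. A reader might infer that the trial has adopted baseline carried forward, or has ruled out nonignorable methods; the text supports neither. What remains is that this is the only method linked to nonignorable dropout, the link runs through a test that cannot work, and no nonignorable variant is stated.

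A reader might also infer that nothing in the plan would reveal the bias. That is wrong for the dilution and the null biases computed above. In those examples dropouts behave like completers, so correctly specified weighting or imputation would recover the true difference and disagree visibly with baseline carried forward. The fair criticism is that these analyses are not committed to, and that they cannot reveal departures of the d·s kind.

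It is tempting, too, to say that the bias favours the intervention because controls have less contact. The article does not say which arm will lose more. A demanding intervention could lose more participants, and the sign would reverse.

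The article also does not say that deaths would be given a carried-forward pressure. Nor is understated variance the main problem: the sample variance of the filled-in outcome is a valid basis for the standard error of that estimator. The fault is bias.

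Finally, imputation details are commonly left to an analysis plan, which is not shown here. Their absence is not the point; the rule that the article does state is.

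**Conclusion.** The point holds in a limited form. The article makes the handling of attrition turn on a distinction that observed data cannot make, and links the nonignorable branch to a method that fixes every dropout's change at zero.

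The dilution, to 7.2 mm Hg at 10% and 6.3 mm Hg at 21%, uses the article's own attrition figures but assumes equal attrition and the same effect in dropouts. If intervention dropouts stop benefiting, the true effect is itself below 8 and the dilution is overstated. The null bias of 0.3 to 1.4 mm Hg rests on assumed falls and assumed attrition splits. At the expected average of 10% with a 1:2 split it is 0.3 to 0.7 mm Hg, small against the standard error of about 2.4. The larger figures need attrition nearer the prior study's 21%, a population the article describes as younger and more mobile.

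This deserves correction because the choice of method is open and could follow the data. It does not by itself undermine the trial.

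**What to change.** - Drop the ignorability test as the condition for choosing a method. Keep the completer and noncompleter comparison, reported by arm, to describe attrition and to choose imputation or weighting predictors.
- Remove baseline carried forward as the answer to nonignorable dropout.
- Commit in advance to one baseline-adjusted primary analysis under missing at random, for example multiple imputation by arm.
- Add one stated nonignorable sensitivity analysis: delta-adjusted imputation taken to a tipping point, or control-based imputation for intervention dropouts.

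The cost is revised wording and slightly more analysis work. Sample size, visits and data collection do not change.
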